### Sample size

The main objective of this study is to demonstrate, in intubated critically ill patients, the superiority of conical cuff shape in reducing abundant microaspiration of gastric contents, compared with standard cuff shape (control group). Based on previous studies [13, 14], the expected incidence of abundant microaspiration of gastric contents is 50 % in control group. We assumed that the use of conical-cuffed tracheal tubes could reduce this incidence to 30 % (that is, an absolute and relative risk reduction of 20 % and 40 %, respectively). To detect this effect size, with a two-sided alpha risk of 5 %, and a power of 80 %, 90 patients would be required per group in a conventional parallel*-*group randomized trial. Since the experimental design is a cluster randomized crossover*,* we adjusted the study sample size to take into account the correlation between outcomes of patients within ICU (namely intraclass correlation coefficient, ICC) [33]. We did not take into account the inter-period correlation (correlation between different patients included within the same ICU but at different periods), in order to maximize the statistical power. Using the formula commonly used to plan a randomized cluster trial by considering each ICU as a pool of two independent clusters (one within each arm), assuming an ICC of 0.035 (corresponding to the upper quartile of ICC values from 31 primary care researches) [34], an expected total number of patients included per ICU of 30 patients, we calculated that 140 patients would be required per group. To account for an anticipated rate of 10 % of patients without any tracheal secretions, we planned to recruit a total of 312 patients.

### Statistical analysis

Statistical analyses will be independently performed by the Biostatistics Department of University of Lille. Data will be analyzed using the SAS software (SAS Institute Inc, Cary, NC, USA), and all statistical tests will be performed with a two-tailed alpha risk of 0.05. Statistical analysis will be performed on an intention-to-treat basis. A detailed statistical analysis plan will be written and finalized prior to the database lock. The final report will be written, based on the CONSORT statement recommendations (Fig. 5).

**Fig. 5 Fig5:**
[figure not shown]
Flow diagram of Best cuff trial according to CONSORT

Baseline characteristics will be compared between the two study groups. Quantitative variables will be expressed as mean (standard deviation), and median (interquartile range). Qualitative variables will be expressed as frequencies and percentages. Normality of distribution will be assessed graphically and using the Shapiro-Wilk test. Chi-square (or Fischer’s exact test), and Student *t*-test (or Mann Whitney test) will be performed to compare qualitative, and quantitative variables, as appropriate.

#### Primary endpoint

The proportion of patients with abundant microaspiration will be compared between the two group using a generalized linear mixed model including group as fixed effect, and center and center*time period as the random effects. Missing data for the primary endpoint are being handled by multiple imputation using chained equations (m = 10 imputations using primary endpoint and patient’s characteristics at inclusion).

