## Methods/Design

### Design

BEST CUFF is a multicenter, cluster randomized crossover controlled and open-label trial performed in patients receiving mechanical ventilation in the ICU. Because tracheal intubation is an urgent procedure in ICU patients, the randomization was performed on the participating ICUs, and not on the patients. These ICUs were randomized into two balanced groups, according to an intervention sequence. Using this design, half of ICUs are randomized to use a PVC conical cuff (Fig. 1) in the first 1-month period and a PVC standard cuff (Fig. 2) in the second 1-month period. The other half of the ICUs will use the two interventions in the reverse sequence.

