**Fig. 2 Fig2:**
[figure not shown]
Standard tracheal cuff

Each ICU recruits distinct subjects during the repeated 2-month periods using the assigned intervention sequence, meaning that each intervention sequence started must be completed (Fig. 3).

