#### Secondary endpoints

A generalized linear mixed model including group as the fixed effect and center and center*time period as random effects will also be used to compare each secondary endpoints between the two groups. For quantitative endpoints, the normality of the model residuals will be checked. In cases of non-normal distribution of residuals (except if a log-transformation could be applied to normalize the data), quantitative endpoints will be compared using a Mann-Whitney *U* test.

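### The planned mixed models have no fixed period effect, so a time shift shared by all ICUs is counted as error; the loss is material only if ICUs complete one or a few sequences

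*Protocol article*

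**What the plan says.** The primary comparison is a generalized linear mixed model "including group as fixed effect, and center and center*time period as the random effects". The paragraph on secondary endpoints repeats the structure: "A generalized linear mixed model including group as the fixed effect and center and center*time period as random effects". Group is the only fixed effect in both.

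In the Design section, half of the ICUs use the conical cuff in the first 1-month period and the standard cuff in the second. "The other half of the ICUs will use the two interventions in the reverse sequence". The same section adds: "Each ICU recruits distinct subjects during the repeated 2-month periods using the assigned intervention sequence". The sequence is therefore repeated. The article does not say how many sequences each ICU completes, or whether time period in the model means the 1-month block or the 2-month sequence.

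A detailed statistical analysis plan is announced but not shown. The article nevertheless lists the model terms outright, so this is a stated choice and not a detail left open.

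**The concern.** Opposite sequences are randomised so that anything affecting all ICUs in the same month (season, case-mix, a change in practice) falls on both tubes and can be removed. Removing it requires a period main effect. The model has the center-by-period interaction but not that main effect. The random interaction is assumed to have mean zero and to be independent between ICUs, so it cannot represent a shift that they share. The shift instead inflates the estimated between-period variance.

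Two things could follow. The standard error becomes too wide, which costs power in a trial planned for only 80%. And if the two sequences contribute different numbers of patients, part of the shift can pass into the estimated tube effect. The secondary endpoints inherit the same structure.

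**Working it through.** **Inputs from the article.** "the expected incidence of abundant microaspiration of gastric contents is 50 % in control group"; the conical cuff "could reduce this incidence to 30"%; the test is planned "with a two-sided alpha risk of 5 %, and a power of 80"%; "assuming an ICC of 0.035"; 30 patients per ICU; ten ICUs; no inter-period correlation; 10% without secretions; enrolment from June 2014 to October 2015.

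**Assumed, because the article does not give them.** A common shift of 0 to 20 percentage points; the split of recruitment between ICUs; the number of sequences per ICU (one, or about eight if recruitment is continuous for 16 months).

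**The plan's own figures.**
- Unadjusted: (1.96 + 0.84)² × (0.25 + 0.21) / 0.20² = 90 per group, as stated. The pooled-variance formula gives 93.
- Design effect: 1 + (15 − 1) × 0.035 = 1.49. 93 × 1.49 = 139, against the stated 140.
- 140 / 0.9 rounds up to 156 per group, or 312 in total, as stated.

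A period term does not enter these figures.

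**Single crossover, ICU-level analysis.** With 280 evaluable patients there are 14 per ICU-period.
- Design effect: 1 + 13 × 0.035 = 1.455.
- Variance of one ICU's difference: (0.25 + 0.21)/14 × 1.455 = 0.0478.
- True standard error over 10 ICUs: √(0.0478/10) = 0.069.

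A shift δ adds +δ to the within-ICU difference in five ICUs and −δ in the other five. Without a period term, the estimated squared standard error becomes 0.00478 + δ²/9:
- δ = 0.10: √(0.00478 + 0.00111) = 0.077.
- δ = 0.20: √(0.00478 + 0.00444) = 0.096.

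Power for the 20-point effect, with a one-sample t-test on the ICU differences (9 df, no period term) against a two-sample t-test between sequences (8 df, period removed):

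| Shift | Power without period | Power with period | Type I error without period |
|---|---|---|---|
| 0 | 73% | 72% | 5% |
| 5 points | 71% | 72% | 4.5% |
| 10 points | 65% | 72% | 3% |
| 15 points | 56% | 72% | 2% |
| 20 points | 44% | 72% | 1% |

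Simulating the mixed model itself (480 runs per setting, z-test, equal ICUs) gives the same direction with a smaller loss. Power without versus with period is 83% vs 87% at 10 points and 73% vs 86% at 20.

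**Bias, single crossover.** If the sequences contribute N₁ and N₂ patients, a patient-weighted difference moves by δ × (N₁ − N₂)/(N₁ + N₂). With 180 vs 100 patients and a 10-point shift this is 10 × 80/280 = 2.9 points. In the simulated mixed model (true log odds ratio −0.847):
- Unequal ICUs, sequences re-randomised in each run: −0.844 without period at 10 points and −0.837 at 20, so no bias on average.
- Large ICUs all in one sequence (180 vs 100): −0.966 without period and −0.883 with it at 10 points.
- The same imbalance with no true effect: −0.10 without and −0.01 with.

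**Repeated monthly alternation.** For 16 months, a linear 10-point trend over the whole trial leaves a gap between odd and even months of only 10/15 = 0.67 points. With the 180 vs 100 split the bias is 0.67 × 80/280 = 0.19 points. In simulation (300 runs per setting):
- Smooth trend, equal ICUs, power without versus with a linear time term: 92% vs 92% at 10 points and 90% vs 91% at 20. With unequal sequences the estimates differ by about 0.01.
- Shift of 10 points aligned with odd/even months, equal ICUs: power 90% with or without an odd/even term.
- The same aligned shift with unequal sequences: log odds ratio −0.981 without and −0.865 with the term.

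**The case against.** The strongest objection is that the large figures belong to a single crossover, while the Design section describes repeated sequences. Over about 16 months each ICU would use each tube in many different months. Season and practice change gradually and do not alternate month by month, so they nearly cancel. This stands, and it is why the expected effect under the described schedule is small.

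A reader might infer that unequal ICU sizes bias the result. The documents do not support that. Bias needs patient totals that differ between the sequences together with a shift that lines up with first and second months, and it averages to zero over the randomisation. The trial still has one realised allocation. The article describes balance by number of ICUs, not of patients, so an imbalance in that allocation cannot be excluded.

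A reader might also infer a raised risk of a false positive. With equal recruitment the omission works the other way, since type I error falls below 5%.

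It is also fair to say that a separate effect for every month would fit poorly: 312/(10 × 16) is about 2 patients per ICU-month. That argues for a sparse period term, not for none. The unseen analysis plan may define time period or add such a term. If it does, the point is settled.

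**Conclusion.** The point holds in a limited form. The stated models leave out the period main effect that the opposite-sequence design makes estimable, and a shared shift then goes into the error.

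- **One or a few sequences per ICU:** the loss is material, about 7 points of ICU-level power for an assumed 10-point shift (65% vs 72%).
- **Repeated monthly alternation as described:** smooth trends cost about a point of power or less. What remains is exposure to bias if a shift aligned with first/second months coincides with unequal sequence totals.

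The size of any shift, the recruitment split and the number of sequences per ICU are assumptions throughout. The stated sample size is unaffected.

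**What to change.** In the model statements for the primary and secondary endpoints:

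1. Define time period as the 1-month block within the repeated 2-month sequence.
2. Add a fixed indicator for first versus second month of the sequence (1 df).
3. Add a low-dimensional calendar-time term, such as linear or quarterly, rather than an effect for every month. A quarterly term alone would not remove a first/second-month shift, so the indicator in step 2 is needed as well.
4. Keep center and center-by-period as random effects.

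The change is wording in the analysis plan, which the article says will be finalised before database lock. If there is no shift, the indicator costs about 1 to 2 points of power (73% to 72% in the single-crossover calculation). The linear time term cost nothing measurable in the 16-month simulation with no trend (92% with or without it, equal ICUs). The cost of quarterly terms was not calculated. The planned 312 patients stand.

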### Data collections

At the time of inclusion, the following baseline characteristics are recorded: age, sex, height, body weight, date of hospital admission, date of ICU admission, patient location before ICU admission (home, hospital for >24 h), date of intubation and mechanical ventilation, preexisting comorbidities (diabetes and COPD, chronic restrictive respiratory failure, chronic heart failure, cirrhosis Child B or C, chronic renal failure, esogastroduodenal reflux, immunosuppression), McCabe score, Simplified Acute Physiology Score II, SOFA score, and reason for the ICU admission.

At the time of randomization, the following characteristics are recorded: SOFA score, duration of enteral feeding before randomization, nasal or oral position of the tracheal tube, cuff shape, and tube size.

During the 48 h following randomization, the variables listed below are recorded: ventilatory mode, mean PEEP, mean airway pressure, mean peak pressure, mean cuff pressure, highest FiO_2_, nitric monoxide use, aerosols, vasopressor support, enteral feeding volume, gastric residual volume, stress ulcer prophylaxis, use of prokinetic agents, vomiting, sedation, neuromuscular blockers, Glasgow Coma Score, mean head of bed elevation, prone position, patient mobilization (on chair), patient mobilization outside ICU room, accidental extubation, reintubation, and death.

Until day 28 or until ICU discharge, the following variables are being collected: sedation, transfusion, tracheotomy, extubation failure, accidental extubation, reintubation, shock, transport outside the ICU, mean head of bed elevation, use of proton pump inhibitors, ICU-acquired infection other than VAP (bacteremia, ventilator-associated tracheobronchitis, intravascular catheter-related infection, urinary tract infection, soft tissue infection, and others), duration of antibiotic treatment, duration of mechanical ventilation, length of ICU stay, death, data related to VAE, pepsin and alpha-amylase levels, VAP, and tracheobronchial colonization (Table 1).

**Table 1 Tab1:** Study flowchart follow-up

	Inclusion	H12 to H72	Until Day 28 or ICU discharge	Suspected VAP
Eligibility : check inclusion and exclusion criteria	X			
Randomization	X			
Quantitative TA culture	X		two times a week	X
Pepsin and amylase measurement in all TA for 48 h		X		
Clinical and radiological signs of VAP			X	
Quantitative TA culture or BAL				X
Clinical data			X	

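### The stated imputation inputs for the primary endpoint do not name randomised group, so read literally the imputed outcomes dilute the treatment effect by about the missing fraction

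*Protocol article*

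**What the plan says.** The Primary endpoint paragraph of the Statistical analysis section fixes two things. The analysis is a "generalized linear mixed model including group as fixed effect, and center and center*time period as the random effects". Missing values of the primary endpoint are "handled by multiple imputation using chained equations (m = 10 imputations using primary endpoint and patient’s characteristics at inclusion". The second statement gives the method, the number of imputations and the inputs. Group, center and period are not among the inputs.

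The Data collections section has two lists that bear on what counts as an inclusion characteristic. The first begins "At the time of inclusion, the following baseline characteristics are recorded: age, sex, height, body weight" and runs to the reason for ICU admission; it contains no cuff shape, ICU or period. The second begins "At the time of randomization, the following characteristics are recorded: SOFA score, duration of enteral feeding before randomization" and ends with "nasal or oral position of the tracheal tube, cuff shape, and tube size". Cuff shape is therefore in the second list. Table 1, however, places randomization in the Inclusion column.

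The Sample size section supplies the planning figures: "the expected incidence of abundant microaspiration of gastric contents is 50 % in control group" and "We assumed that the use of conical-cuffed tracheal tubes could reduce this incidence to 30" %. It also allows 10 % for "patients without any tracheal secretions, we planned to recruit a total of 312 patients".

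**The concern.** An imputation model should contain at least the terms of the model that will be fitted to the completed data. If the tested exposure is left out, missing outcomes in both arms are filled in from the same distribution. The completed data are then a mixture of observed patients, who show the treatment effect, and imputed patients, who do not. The estimate moves toward zero.

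The trial was sized for 80 % power, and recruitment was raised from 280 to 312 to absorb the anticipated 10 %. An imputation that omits group would give back part of that protection. The article also presents microaspiration as a step before larger studies of VAP, so an understated effect or a missed one could misdirect that decision.

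The center and center-by-period terms raise a related but different issue. Imputing without them ignores the within-ICU correlation that the mixed model is meant to represent.

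**Working it through.** **Inputs (Sample size section).** Control risk 0.50; conical-cuff risk 0.30; two-sided alpha 0.05; power 0.80; ICC 0.035; 30 patients per ICU, hence 15 per ICU and arm; 10 % anticipated without secretions. That 10 % is used here as the missing fraction, because it is the only such figure given.

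**The plan's own figures reproduce.**
- Unadjusted size with unpooled variance: (1.960 + 0.842)² × (0.25 + 0.21) / 0.20² = 90.3, against 90 stated. The pooled-variance formula gives 93.
- Design effect: 1 + (15 − 1) × 0.035 = 1.49. Then 91 × 1.49 = 136 and 93 × 1.49 = 139, against 140 stated.
- Allowance: 140 / 0.90 = 155.6, rounded up to 156 per group, or 312 in total, as stated.

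**Dilution when group is not in the imputation model.** With equal groups, the pooled risk is (0.50 + 0.30) / 2 = 0.40. Let m be the missing fraction, equal in both arms.
- Control: (1 − m) × 0.50 + m × 0.40
- Conical: (1 − m) × 0.30 + m × 0.40
- Difference: (1 − m) × 0.20

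At m = 0.10 the control rate is 0.45 + 0.04 = 0.49 and the conical rate is 0.27 + 0.04 = 0.31, a difference of 18 points. The odds ratio moves from (0.30/0.70) / (0.50/0.50) = 0.43 to (0.31/0.69) / (0.49/0.51) = 0.47.

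| Missing fraction | Expected difference without group |
|---|---|
| 5 % (assumed) | 19 points |
| 10 % (protocol) | 18 points |
| 15 % (assumed) | 17 points |
| 20 % (assumed) | 16 points |
| 30 % (assumed) | 14 points |

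**Simulation with ICU structure.** There were 10 ICUs with 16 patients per ICU and arm, ICC 0.035, outcomes missing completely at random, and m = 10 imputations. Paired ICU-level risk differences were pooled by Rubin's rules and tested with t on 9 df, in 3,000 runs per cell. No baseline covariates were simulated. Neither imputation model contained ICU or period, so the two differ only in group.

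| 10 % missing | Without group | With group |
|---|---|---|
| Mean difference | 17.9 points | 20.0 points |
| Power | 67 % | 75 % |
| Type I error (both risks 0.40) | 3.4 % | 4.3 % |

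Adding group alone restores the 20 points. Leaving out ICU and period did not bias the estimate.

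**Second simulation, without ICU structure.** With an effective size of 156 / 1.49 ≈ 105 per group and 10 % missing, the estimate was 17.6 points without group and 19.6 with it. Power was 73 % and 79 %. Without group, the average model standard error was 0.070 against an empirical 0.062, so Rubin's variance was too large. This fits the type I error below 5 % in the first simulation.

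**The case against.** The strongest reply is that the exclusion of group is inferred from a short parenthesis that does not say only. The document does not keep inclusion and randomization apart. ICUs, not patients, were randomised. The 48 h window is counted from inclusion in the Definitions and Primary endpoint sections but from randomization under Data collections. SOFA is in both lists, and Table 1 puts randomization in the Inclusion column. Intubation with the study tube is itself an inclusion criterion, so cuff shape is known at inclusion. The article also defers detail to a statistical analysis plan that is not shown.

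Much of this stands. The documents support saying that group is not named; they do not establish that it will be left out. It does not dispose of the point, because the paragraph specifies the inputs, lists even the variable being imputed, and does not mention the tested term. Randomised group is not a natural reading of a patient characteristic, and center and period are in neither list.

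Three stronger readings are tempting but unsupported:
- **That omitting ICU and period also pulls the result toward zero.** The estimate stayed at 20.0 points without them.
- **That the plan risks a false claim of superiority.** The error is conservative, with type I error of about 3 % in the simulation.
- **That patients with no secretions will be imputed as having abundant microaspiration.** The article never says that they will be imputed, and the sample-size allowance is consistent with treating them as non-evaluable. How to count them is a separate question about what is being estimated.

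**Conclusion.** The point holds in a limited form, at moderate severity. The stated inputs are narrower than the analysis model and do not name the exposure under test. If they are followed literally, the expected difference shrinks from 20 to 18 points at 10 % missing, with roughly 6 to 8 points of power lost and no inflation of type I error. The wider range of 19 to 14 points rests on assumed missingness of 5 to 30 %, which the article does not give.

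These sizes assume the planned 50 % and 30 % risks, equal missingness in the two arms, outcomes missing completely at random, and baseline characteristics that carry no information about group. The simulations analysed risk differences and not the planned mixed model, so the power figures are approximate. The dilution itself follows from simple algebra.

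For center and period, the finding is inconsistency with the clustering in the analysis model. It mainly concerns the standard error, and its size was not estimated.

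**What to change.** Reword the sentence on missing data along these lines: the imputation model for the primary endpoint will include randomised group and will account for ICU and ICU-period, together with the primary endpoint and the baseline characteristics, in line with the analysis model. Carry the same wording into the statistical analysis plan before database lock. If that plan already includes group, the published text only needs to be brought into agreement with it.

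The cost is one sentence and a few extra terms in the imputation procedure. No further data are needed. A sensitivity analysis for patients without secretions may be added, but it is optional and not needed to correct this error.
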